**Table 1 Tab1:** **Indicators followed in baseline and follow-up survey**

Indicators	Measures	Methods
Behavioral	Tobacco	Questionnaire
	Alcohol*	
	Physical activity	
	Salt consumption	
Anthropometric	Height	Stadiometer
	Weight	Weighing machine
	Waist circumference	Measuring tape
	Blood pressure	Electronic BP monitor
Treatment history, Health services, Health care costs	Compliance	Questionnaire
	Awareness, Risk factor control	
	Service utilization	
	Treatment cost	

*: Not covered in Tibet, China site.

The primary outcome will be the net difference between the intervention and control groups in the pre- and post-intervention change in the proportion of high-risk individuals treated with anti-hypertensive medication, obtained through the two surveys described above. This process indicator is chosen for its close association with the intervention scheme, effect on lowering high blood pressure, and its excellent power.

A number of secondary outcomes will also be evaluated, including the net difference between the intervention and control groups in the pre- and post-intervention change in the proportion of high-risk individuals treated with aspirin, the net difference in mean blood pressure from baseline to follow-up in high-risk individuals between the intervention and control villages, as well as hypertension awareness, treatment, and control rates. Awareness of modifiable lifestyle risk behaviors will also be assessed, specifically on the proportion of high-risk individuals aware of the harms of smoking and consumption of a high salt diet. Finally, the proportion of high-risk individuals receiving five or more follow-up visits from CHWs will also be calculated.

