### Sample size

Key underlying assumptions for this study are that there will be 20 intervention villages and 20 control villages with 50 consenting high-risk patients in each village and an estimated total of 2,000 high-risk individuals, an intra-cluster correlation coefficient (ICC) of 0.01 or 0.02
[36, 47], and two-sided alpha of 0.05. For the primary outcome, assuming the proportion of anti-hypertensive medication prescriptions in the control villages is 20% (conservative as preliminary data shows it to be <10% in the target study sites), the power to detect a 10% difference in the primary outcome of anti-hypertensive medication use is excellent (>90%) with an ICC of 0.01, and similarly high with an ICC of 0.02. Assuming a standard deviation of change in systolic blood pressure of 15 mmHg among the high-risk individuals, the power to detect a 3 mmHg net difference in this secondary outcome between the intervention and control group pre-post differences will be >90% with an ICC of 0.01 (>90% as well if ICC = 0.02).

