### Statistical analysis

All analyses will be conducted at individual level according to intention-to-treat principles, and take into account the stratification design and cluster effects. For the primary outcome, anti-hypertensive medication use, log-binomial models with random effects for villages to account for clustering and random effects for intercept to account for the pre-post correlations within individuals and a fixed effect for country to account for the stratified study design will be used. Other than the main effect from intervention and time, an interaction term between intervention and time will be added in the model to test if the slope of the pre-post changes differs by intervention or control group. To account for the heterogeneity between two countries, the two-way interaction of the country variable with intervention and time will be included into the above models. In the case of significant interaction existing, the separate analysis by country will be conducted afterward. The net effect from intervention will be reported as difference-in-difference of proportions together with model-based 95% confidence intervals obtained by transforming back from models. For continuous outcomes, such as systolic blood pressure, similar strategies will be adopted but linear models instead of log-binomial models will be used. Some adjusted analysis will also be performed to account for potential unbalanced baseline information. Other pre-specified subgroup will include analyses by sex and age (40–59 vs. 60 years or older) using similar strategy for the country variable.

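### The country heterogeneity check names two-way interactions, but the net effect is already intervention × time, so the trigger for separate country analyses can respond to the wrong quantity

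*Protocol article*

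**What the plan says.** The primary outcome (Outcome evaluation, paragraph after Table 1) is the "net difference between the intervention and control groups in the pre- and post-intervention change in the proportion of high-risk individuals treated with anti-hypertensive medication". The Statistical analysis section gives this quantity its model term: "an interaction term between intervention and time will be added in the model to test if the slope of the pre-post changes differs by intervention". It then deals with heterogeneity between the countries: "the two-way interaction of the country variable with intervention and time will be included into the above models". The next sentence gives the consequence: "In the case of significant interaction existing, the separate analysis by country will be conducted afterward". On reporting: "The net effect from intervention will be reported as difference-in-difference of proportions together with model-based 95% confidence intervals". The last sentence of the section extends the approach to "analyses by sex and age (40–59 vs. 60 years or older) using similar strategy for the country variable". The article names no interaction of country, intervention and time together.

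**The concern.** The effect of interest is a difference in differences, so it is already a two-way interaction. Asking whether it differs by country adds a third factor. The two terms that the text names answer other questions. Country × time compares the overall pre-post trend in Tibet with that in Haryana. Country × intervention compares the arm gap averaged over both surveys, which includes any baseline gap. A rule built on them can announce heterogeneity when the net effects are equal, and can weaken when they differ.

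This matters because the article prescribes an action on the result, and because a country-specific trend is plausible here. In India only, the study drugs are also supplied to facilities serving control villages (‘2 + 2’ intervention model section). The article gives no size for any such trend.

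**Working it through.** **Inputs from the article.** "20 intervention villages and 20 control villages with 50 consenting high-risk patients in each village"; 20 villages per country; ICC 0.01 or 0.02; two-sided alpha 0.05; control proportion 20%; target difference 10 points. **Assumed:** pre-post correlation ρ of 0.3 to 0.5, and the illustrative cell proportions below.

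**Stated power first.** Design effect DE = 1 + 49 × ICC = 1.49 or 1.98. Effective size per arm is 1000/DE = 671 or 505. For 20% vs 30% the power is 98.9% or 95.7%, in line with the article's claim. This does not depend on the present point.

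**What the two-way terms estimate.** In country c, let T be the control-arm change, B the baseline arm gap (intervention minus control), and D the net effect. The intervention-arm change is T + D and the follow-up gap is B + D. In a balanced linear model without the three-way term:

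- country × time = (T₂ − T₁) + ½(D₂ − D₁)
- country × intervention = (B₂ − B₁) + ½(D₂ − D₁)
- the three-way term, if fitted, = D₂ − D₁

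Each two-way term therefore carries half of the heterogeneity plus something else, and the other part can create a signal or cancel one.

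**Equal effects, different trends.** Country A: control 20→20%, intervention 20→30%. Country B: 20→30% and 20→40%. The net effect is 10 points in both. For a change from p to q, v = p(1−p) + q(1−q) − 2ρ√[p(1−p)q(1−q)], and V is the mean of v over the two arms. With ρ = 0.3, V_A = (0.2240 + 0.2600)/2 = 0.2420 and V_B = (0.2600 + 0.2824)/2 = 0.2712. With 1000 people per country and ICC 0.01, SE = √[(0.2420 + 0.2712) × 1.49/1000] = 0.0277. Power = Φ(0.10/0.0277 − 1.96) = Φ(1.66) = 0.951. The same formula gives:

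| Trend gap | ICC 0.01, ρ 0.3 | ICC 0.01, ρ 0.5 | ICC 0.02, ρ 0.3 | ICC 0.02, ρ 0.5 |
|---|---|---|---|---|
| 10 points | 0.951 | 0.989 | 0.880 | 0.959 |
| 5 points | 0.449 | 0.580 | 0.355 | 0.466 |

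**Simulation of the whole rule.** Village means on a linear scale, 10 villages per arm per country, 50 people each, ICC 0.02, ρ = 0.5, 3,000 runs, 5% tests:

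| Scenario | Either two-way term significant | Three-way term significant |
|---|---|---|
| No country difference | 9% | 5% |
| Equal net effects, trends 10 points apart | 95% | 6% |
| Equal net effects, 8-point baseline arm gap in one country | 42% | 5% |
| Net effects 20 vs 0, flat controls, balanced baseline | 97% | 96% |
| Net effects 20 vs 0, control rising 10 points in the zero-effect country | 54% | 95% |
| As the previous row, plus a 10-point baseline arm gap there | 7% | 94% |

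The baseline-gap rows deserve less weight than the trend rows. With ICC 0.02, the standard error of a baseline arm gap within one country is √(2 × 0.16 × 1.98/500) = 0.036, so 8 points is about 2.2 standard errors and randomization would seldom produce it.

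**Scale.** The primary model has a log link, but the result is reported as a difference of proportions. With flat controls, 20→30% and 10→20% are both +10 points, yet the log three-way contrast is ln 2.0 − ln 1.5 = 0.29. In the 10-point trend example above it is ln(0.4/0.3) − ln(0.3/0.2) = −0.12. A three-way term read on the log scale is therefore not zero when the reported effects are equal.

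**The case against.** The best defence is that this is a condensed article and the phrase is loose. It is singular, follows directly after the intervention × time term, and may have meant country crossed with that term; a model equation would normally sit elsewhere. That may be the intent, but calling the interaction two-way contradicts it, so the sentence needs correcting on either reading. It is a stated rule and not a detail left for later.

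Four stronger conclusions are tempting, and the article does not support them.

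- **That the two-way terms cannot see heterogeneity.** They carry half of it each. With flat controls and net effects of 15 vs 5 points, a village-level simulation (ICC 0.01–0.02, ρ 0.3–0.5) had the two-way rule firing in 48–68% of trials against 35–57% for the three-way term.
- **That the rule decides between one pooled answer and two country answers.** The country analyses are described as following afterward, and the article still commits to reporting the net effect. Nothing says that the pooled result is dropped. Randomization was stratified by country, so each country estimate remains a valid randomized comparison.
- **That under a three-way reading the reported effect would be that of the reference country.** The article reports a back-transformed difference-in-difference and not a raw coefficient, and that can be averaged over countries.
- **That the three-way test solves the power problem.** With net effects of 15 vs 5 points and control changes of 0 and +5, the same kind of simulation gave 31–55% for the three-way term and 24–29% for the two-way rule. The gain is mainly in specificity and in resistance to masking.

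It is also fair that a 10-point trend gap equals the whole target effect and that no document supports a figure. The percentages are illustrations.

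**Conclusion.** Wrong as written. The rule tests terms that are not the country difference in the net effect. Its main weakness is non-specificity: 88–99% false triggering for an assumed 10-point trend gap and 36–58% for 5 points, and about 9% with no country difference at all because either of two terms can fire. Its second weakness is masking when control trends oppose the heterogeneity (54% against 95% in the example with net effects of 20 vs 0). These figures rest on the article's cluster numbers and ICCs, on assumed cell proportions and ρ, and on a linear risk scale; log-link results would differ somewhat. The consequence is misdirected statements about country, sex and age differences. A reader might infer that the primary result is biased or underpowered; nothing here shows that.

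**What to change.** Replace the heterogeneity sentence so that it:

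1. keeps all lower-order terms and adds country × intervention × time (sex or age × intervention × time for the subgroups);
2. bases the heterogeneity statement and the country-specific analyses on that contrast alone, at a stated test level;
3. judges it on the reported scale, as the between-country difference in the back-transformed difference-in-difference of proportions, or says explicitly that the log scale is used;
4. takes the overall effect from the model without the three-way term, or as a pre-specified average of the two country effects.

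The cost is a small edit to the Statistical analysis section before analysis, with no new data or participants.

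### The primary effect is tested as a ratio of risk ratios but defined, powered and reported as a difference-in-difference of proportions, so the p-value and the confidence interval can disagree

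*Protocol article*

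**What the plan says.** Under Outcome evaluation, the primary outcome is additive: "The primary outcome will be the net difference between the intervention and control groups in the pre- and post-intervention change in the proportion" of high-risk people on antihypertensive medication. The Sample size section powers a 10% difference in that proportion with "20 intervention villages and 20 control villages with 50 consenting high-risk patients in each village", "an intra-cluster correlation coefficient (ICC) of 0.01 or 0.02", and "two-sided alpha of 0.05".

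The Statistical analysis section specifies a log-binomial model with random intercepts for village and person, fixed effects for country, intervention and time, and two-way interactions of country with intervention and time. The only test of effect it names is the interaction: "an interaction term between intervention and time will be added in the model to test if the slope of the pre-post changes differs" between groups. The estimate is then put on another scale: "The net effect from intervention will be reported as difference-in-difference of proportions together with model-based 95% confidence intervals obtained by transforming back from models". The section names no test of the difference-in-difference itself. It does not say whether predicted proportions are averaged over the random effects.

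**The concern.** With a log link, the exponentiated intervention-by-time coefficient is the intervention arm's follow-up/baseline risk ratio divided by the control arm's. The primary outcome is instead a difference between two changes in proportions. These are different functions of the same four proportions, and they can point in different directions when the arms start at different levels and use changes over time. The model includes an intervention main effect, so any observed baseline difference enters both contrasts.

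At stake is the primary result. A p-value above 0.05 could stand beside an interval that excludes zero, or the reverse, and the text does not say which governs. The power statement also belongs to the difference scale, not to the test named. Finally, in a log-link model with normal random intercepts, back-transforming the fixed effects alone gives proportions for a person and village at random effect zero, and these lie below the population proportions.

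**Working it through.** **1. The plan's own power figure.** Inputs from Sample size: 1,000 per arm (20 × 50), control 20%, difference 10 points, two-sided 0.05. The design effect is 1 + 49 × ICC = 1.49 or 1.98, so the effective n per arm is 671.1 or 505.1. A two-proportion test of 20% against 30% has power 98.9% (ICC 0.01) and 95.7% (ICC 0.02); a t reference on 38 df gives 98.6% and 94.9%. The stated figures reproduce, for a simple difference of proportions.

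**2. The two scales on one set of proportions.** Let control use rise from 10% to 20% and let the intervention arm start at 12%.
- Ratio of ratios = 1 requires 12% × 2 = 24% at follow-up. The difference-in-difference is then (24 − 12) − (20 − 10) = +2 points.
- Difference-in-difference = 0 requires 22% at follow-up. The ratio of ratios is then (22/12)/(20/10) = 0.92.
- With equal baselines of 10%, both nulls give 20% at follow-up and coincide.

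The SE of the baseline difference is √(2p(1 − p)/n_eff). At p = 10% and ICC 0.01 it is √(0.18/671.1) = 1.6 points; at p = 20% and ICC 0.02 it is √(0.32/505.1) = 2.5 points. At 10% use, a 2-point gap is therefore little more than one SE (1.6–1.9 points). A starting level of 10% or lower is realistic here: "preliminary data shows it to be <10% in the target study sites".

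**3. How often the two tests disagree.** A 6,000-run cluster simulation applied village-level Wald tests on both scales (ICC 0.02, assumed pre-post correlation 0.3). The share of trials in which exactly one test was significant was:

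| Control trend | True effect | Disagree |
|---|---|---|
| 10%→10% | 0 | 0.6% + 0.5% = 1.1% |
| 10%→20% | 0 | 2.9% + 3.0% = 6.0% (unrounded 0.0293 + 0.0303) |
| 20%→30% | 0 | 1.8% + 2.3% = 4.1% |
| 10%→15% | 5 points | 3.0% + 17.1% = 20.1% |

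In the second row the two estimates had opposite signs in about 20% of trials. In the last row most disagreements (17.1%) were trials in which the difference was significant and the ratio was not. A second simulation, with ICC 0.02 and a moderate assumed correlation, gave about 5% and 20% for the second and last rows, with both tests holding about 5% error.

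**4. Power on each scale, equal baselines.** Take 20%→20% against 20%→30%, ICC 0.02 and assumed correlation ρ = 0.3, with the design effect applied to the change.
- Difference: the variance of a change is p₀q₀ + p₁q₁ − 2ρ√(p₀q₀p₁q₁), which is 0.224 (control) and 0.260 (intervention). SE = √(0.484/505.1) = 0.0310; z = 0.10/0.0310 = 3.23; power 89.8%.
- Log ratio: the variance is q₀/p₀ + q₁/p₁ − 2ρ√((q₀/p₀)(q₁/p₁)), which is 5.60 and 4.50. SE = √(10.10/505.1) = 0.1414; z = ln(1.5)/0.1414 = 2.87; power 81.8%.

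With ρ = 0.5 the figures are 96.8% and 92.2%. The second simulation gave about 93% and 85%. The first gave 92.67% + 3.35% = 96.0% and 92.67% + 0.02% = 92.7%, a gap of about 3 points. The direction is consistent across these settings; the size depends on correlations that the article does not give.

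**5. Back-transformation at random effect zero.** With a log link and total random-intercept variance s², the population proportion is exp(η + s²/2), so exp(η) is that proportion times exp(−s²/2). Matching the correlation r gives exp(s²) − 1 = r(1 − p)/p, hence a factor of [1 + r(1 − p)/p]^(−1/2). A true 10-point net difference becomes:
- Village variance only (r = ICC). At p = 20%: 1.04^(−1/2) = 0.981, 9.8 points (ICC 0.01); 1.08^(−1/2) = 0.962, 9.6 points (ICC 0.02). At p = 10%: 9.6 and 9.2 points.
- Village plus person, with r an assumed pre-post correlation of 0.1, 0.3 or 0.5. At p = 20%: 1.4^(−1/2) = 0.845, 2.2^(−1/2) = 0.674 and 3^(−1/2) = 0.577, so 8.5, 6.7 and 5.8 points. At p = 10%: 7.2, 5.2 and 4.3 points.

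The ratio of ratios does not change. Averaging over the random effects largely removes the loss: with a total SD of 0.5 and probabilities capped at 1, the zero-effect difference is 26.5% − 17.7% = 8.8 points and the averaged one is 29.95% − 20.01% = 9.9 points. The lognormal form is approximate at large variance, because about 2% of people would have an implied probability above 1 at p = 20% and ρ = 0.5.

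**The case against.** The best defence is that this is a randomised trial with allocation concealed until baseline collection ends. Expected baselines are equal, the two nulls then coincide, and the interaction test is valid. That stands. A reader might infer that the named test has the wrong null or an inflated error rate; the documents do not support this, and the simulations show similar error rates on both scales. Without a trend or an effect, disagreement is about 1%. The 10%→20% setting needs control use to double within a year, and the 20% figure arises under a true effect, so it largely reflects a power difference. What remains is that the reported interval and the named test answer different questions in realistic trials.

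A second defence is that transforming back can naturally mean predicting the four arm-by-time proportions and contrasting them. Nothing says that the interaction coefficient is exponentiated and called a difference, and averaging over random effects is detail that an article may leave to the analysis plan. That also stands. A reader might infer that the plan will shrink the reported effect by some 40%; the text does not fix prediction at random effect zero, and a factor of 0.58 needs a correlation of 0.5 that the article does not give.

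A reader might also infer that the model will fail to converge and force an unplanned replacement. No fit has shown this, and a fallback may well be in an analysis plan that is not shown.

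**Conclusion.** The concern holds as a mismatch between stated rules: outcome, power, estimate and interval are on the difference scale, while the only named test of effect is on the ratio scale. It does not invalidate the test. The consequence is a primary p-value and interval that can conflict, in about 5–6% of null trials with a 10%→20% trend and about 20% with a 5-point effect over a 10%→15% trend. In the settings examined the named test also has lower power: 82–85% against 90–93% at ICC 0.02, with a gap of about 3 points in one simulation. These figures assume a pre-post correlation near 0.3.

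The shrinkage is conditional on predicting at random effect zero. Its direction is then certain under normal random intercepts. Its size is 2–8% from the stated ICC alone; anything larger depends on an assumed pre-post correlation.

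**What to change.** State in the Statistical analysis section that the primary p-value and 95% interval both come from the same population-averaged difference-in-difference of proportions. Obtain the four arm-by-time proportions by marginal standardisation, averaging over the random effects and over the covariates, including country, and use a delta-method or village-level bootstrap interval. An identity-link GEE clustered on village with a small-sample correction is one acceptable alternative. Report the ratio of risk ratios as supportive. The cost is a few sentences and slightly more programming; design, data collection and sample size do not change.

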### Process and economic evaluation

Process evaluation will be conducted at the end of the intervention program to investigate the extent to which the intervention has been implemented as designed, and to identify the facilitators and barriers to the implementation of the intervention program at each level of the study. We will conduct face-to-face, semi-structured interviews by independent interviewers. Interviewees include the CHWs, high-risk individuals in the selected villages, local project administrators, and government officials. A standardized interview guideline will be developed that contains a mixture of close- and open-ended questions. All interviews will be audio-recorded, transcribed and analyzed using a qualitative descriptive interpretive approach combing thematic content analysis and constant comparison methods facilitated by QSR NVIVO 10.0 data management software. The economic evaluation will help determine the economic feasibility of expanding such an intervention using data collected on healthcare services usage and medication use as obtained from the follow-up surveys.

